#### *Sample size – calculations and conclusions*

We estimate that a sample size of 100 participants in each arm would give power of at least 80% to detect differences in primary and secondary endpoints of a magnitude consistent with published results from similar studies. Inclusion of provision for a 20% drop out rate could potentially lead to powers of near 90% or more if the assumption of a drop rate of 20% was too pessimistic.

|                          |            |               |            |       |          |
|--------------------------|------------|---------------|------------|-------|----------|
| Trial name:              | IMPRESS-AF |               |            |       |          |
| Protocol version number: | 6.0        | version date: | 12/10/2015 | Page: | 47 of 67 |

---

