### 2.2 Outcome Measures

The **Primary** efficacy end point will be the improvement in exercise tolerance at 2 years. This will be assessed by the difference between trial groups in peak VO2 on CPET.

The **Secondary** efficacy end point will be the level of improvement in quality of life and diastolic function, and also the improvement the rate of all-cause hospital admissions and spontaneous return the sinus rhythm, with spironolactone. This will be assessed by:

- a) improvement in exercise tolerance measured by 6-minute walking test (a simple test of exercise performance) at baseline and at 2 years
- b) improvement in quality of life (using the validated Minnesota Living with Heart Failure [MLWHF] and EuroQol EQ-5D-5L [EQ-5D] questionnaires self-completed by participants, which will be completed at each months 12 and 24)
- c) improvement in LV diastolic function (E/E' on echocardiography) will be assessed at baseline and at 2 years
- d) improvement in rates of all-cause hospitalisations during 2 year follow-up.
- e) spontaneous return to sinus rhythm (ECG) after 2 years of treatment.

---

|                          |            |               |            |       |          |
|--------------------------|------------|---------------|------------|-------|----------|
| Trial name:              | IMPRESS-AF |               |            |       |          |
| Protocol version number: | 6.0        | version date: | 12/10/2015 | Page: | 17 of 67 |

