**Figure 3. Gantt chart for the IMPRESS-AF trial.**

## 8.2 Trial Procedures

### Establishment of permanent AF

Permanent AF will be defined in accordance with the ESC criteria as a cardiac arrhythmia with the following characteristics: (1) The surface ECG shows 'absolutely' irregular RR intervals; (2) There are no distinct P waves on the surface ECG; (3) The atrial cycle length (when visible), is usually variable and <300 bpm; (4) duration of the AF >12 months with no plans in place for pharmacological or electrical cardioversion (rate control approach)

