Secondary analyses will also use linear or non linear mixed modelling as above but with dependent variable the secondary end points mentioned in the earlier Trial End Points section Interactions between intervention/control, and age and gender will also be included in the mixed modelling analyses to see whether differences in secondary endpoints between intervention and control participants vary with these two factors. Each mixed model analysis will be run additionally separately on each stratum. The primary QoL analysis will be the change in the overall QoL score between treatment groups over the two year duration. This will include baseline measures as a covariate. Full analysis will therefore be completed at the 24 months period and this will form the principle QoL analysis. The 12 month QoL assessments will allow a preliminary analysis to be undertaken to determine if changes occur within the first 12 months. These repeated measures will allow further exploratory analysis of changes in QoL to be undertaken to explore which domains are driving the changes in the QoL scores.

3. Missing values will be substituted using a multiple imputation procedure. Because of the likelihood of non normality the method of Hussain will be used. This replaces the data by its Normal scores, imputes using these transformed data and then uses a polynomial relationship between Normal scores and untransformed data to give a complete set of data. This is then repeated 10 times and variation seen between repetitions and within are used to estimate the uncertainty in the imputed mean value.

In the case of missing data due to death of the participant during the trial a comparative analysis will be conducted between surviving participants and the deceased. If no difference is apparent then MI will be performed on all of the data but otherwise a complete case analysis will be conducted and a report compiled setting out the difference between the deceased and the surviving participants.

|                          |            |               |            |       |          |
|--------------------------|------------|---------------|------------|-------|----------|
| Trial name:              | IMPRESS-AF |               |            |       |          |
| Protocol version number: | 6.0        | version date: | 12/10/2015 | Page: | 45 of 67 |

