### 13.1.1 Power Calculations

We will send invitations to 1280 potential participants from 64 GP practices with the aim of recruiting 640 for further testing. 250 of the screened participants will then be randomised. In addition, suitable participants from outpatient clinics run by [name] and [name] will also be invited to take part.

Our primary outcome will be based on a 'gold' standard test of exercise tolerance defined by peak  $\text{VO}_2$  using CPET and assessed at baseline and after the treatment with the trial drug. We hypothesise that the spironolactone will improve peak  $\text{VO}_2$  compared to the placebo treated subjects. We base our power calculation for peak  $\text{VO}_2$  on the published values of peak  $\text{VO}_2$  in subjects with HFpEF ( $16 \pm 5$  ml/min/kg). We anticipate a difference of 2ml/min/kg in the improvement in peak  $\text{VO}_2$  after 2-year treatment with spironolactone compared with the control group. Unfortunately this publication does not give a standard deviation on the change in peak  $\text{VO}_2$  from baseline but a similar trial, Edelmann et al provides that statistic (5 ml/min/kg) and also reports a similar magnitude of effect.

A sample size of 100 patients in each group will have 80% power to detect a difference in means of 2.000 assuming that the common standard deviation is 5.000 (effect size =0.40) using a two group t-test with a 0.05 two-sided significance level. Sample size calculation was conducted using the nQuery software. Approximately, for 80% power at 5% significance, sample size in each group would be  $15.68/(\text{effect size})^2$ . To accommodate a loss to follow-up of 20% of patients from each group would imply initially recruiting a total sample size of 250 ( $250 \times 0.8 = 200$ ) in order to still retain 200 patients in all. Loss of 20% of patients would still enable effects in excess of 2.3ml/min/kg (effect size=0.46) to be detected with 90% power at the 5% significance level. Sample size= $21.0/(\text{effect size})^2$  for 90% power, 5% significance. At the other extreme zero loss to follow up from 250 patients would lead to 88% power to detect a 2 ml/min/kg at 5% significance Prediction of 20% loss to follow up is based on a 10% loss per year and composed of 5% due to death and 5% due to other reasons. The relevant population of patients would be under regular follow up and as such would have relatively lower expected mortality.

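### The claim of at least 80% power for the secondary endpoints has no calculation behind it for return to sinus rhythm or EQ-5D, and for sinus rhythm it is unlikely to hold for modest effects

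*Protocol*

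**What the plan says.** Section 2.2 lists five groups of secondary measures. They include EQ-5D, under quality of life, and "spontaneous return to sinus rhythm (ECG) after 2 years of treatment". Section 8.2 defines the permanent AF required for entry as including "duration of the AF >12 months with no plans in place for pharmacological or electrical cardioversion (rate control approach").

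Section 13.1.1 works out power for peak VO2, 6-minute walk distance, E/e' and MLWHFQ, and states a detectable reduction for all-cause admissions. Its conclusion is then general: 100 per arm "would give power of at least 80% to detect differences in primary and secondary endpoints", provided the effects match published results from similar studies.

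For analysis, section 13.1 says: "Secondary analyses will also use linear or non linear mixed modelling as above but with dependent variable the secondary end points". The model referred to has baseline peak VO2, age, gender, systolic and diastolic blood pressure and BMI as covariates, with GP practice or recruitment centre as a random effect. For the secondary endpoints, section 13.1 adds treatment-by-age and treatment-by-gender interactions, and runs every model again within each randomisation stratum. No endpoint is exempted.

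**The concern.** The conclusion covers more endpoints than the calculations before it. For sinus rhythm, the protocol gives a hypothesised direction (section 1.2) but no placebo rate, target difference or published effect. The condition about published magnitudes therefore has nothing to refer to for this endpoint. The same is true of EQ-5D.

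Sinus rhythm matters more because it is binary and probably uncommon in a population selected for long-standing AF under rate control. If the sentence stands, a null rhythm result could be reported as coming from a trial with 80% power for it. Separately, a model with many terms fitted to few conversions can show separation (an infinite odds ratio) or fail to converge, so following the text literally might give no usable estimate.

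**Working it through.** **1. The plan's own figures.** Inputs from section 13.1.1: two-sided 5% test ("using a two group t-test with a 0.05 two-sided significance level"), 100 evaluable per arm, difference 2 ml/min/kg, SD 5.

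- Peak VO2: effect size 2/5 = 0.40. The protocol's formula gives 15.68/0.40² = 98 per arm. The t-test power at 100 per arm is 80.4% (stated 80%).
- 6-minute walk, 26 m with SD 48: about 97% (stated 96%).
- E/e', 3.2 with SD 2.08: over 99% (as stated).
- MLWHFQ, 5 with SD 11.35: about 87% (as stated).

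These four reproduce.

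**2. Admissions.** The protocol gives n = 7.84 × (R1 + R2)/(R1 − R2)² and says that a reduction of 15% or more is detectable from a rate of about 20%. It does not say whether 15% is relative or absolute.

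- Relative, 20% to 17%: 7.84 × 0.37/0.03² = 3,223 per arm.
- Absolute, 20% to 5%: 7.84 × 0.25/0.15² = 87 per arm.

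The claim therefore depends on the reading, and admissions cannot be listed as an endpoint whose calculation holds until that is settled.

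**3. EQ-5D.** No difference, SD or source is given. The general result in step 1 means that any roughly normal continuous endpoint has 80% power for a standardised difference of 0.40 at 100 per arm. Whether EQ-5D could show a difference of that size is not discussed.

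**4. Sinus rhythm.** There is no stated figure to reproduce. I **assume** a 2-year placebo rate of 0%, 1%, 2% or 5%. Power is the sum, over all pairs (x, y) of conversions in two independent binomials with n = 100, of the probability of each pair for which the test gives p < 0.05.

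| Placebo rate | Spironolactone rate for about 80% power, uncorrected chi-square | Expected conversions in 200 | Fisher power at the same rates |
|---|---|---|---|
| 0% | 5.5% | 5.5 | 47% |
| 1% | 9.5% | 10.5 | 73% |
| 2% | 11.5% | 13.5 | 72% |
| 5% | 17% | 22 | 73% |

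Check on the first row: 4 versus 0 gives chi-square = 200 × (4 × 100)²/(100 × 100 × 4 × 196) = 4.08, above 3.84, so four conversions suffice. P(at least 4 of 100 at 5.5%) = 81%. Fisher's test needs six (5 versus 0 gives p = 0.059; 6 versus 0 gives 0.029).

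The usual normal-approximation formula asks for somewhat more: about 7.5%, 10.0%, 12.1% and 17.4%. The message is the same.

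| Doubling of the rate | Chi-square power | Fisher power | Expected conversions in 200 |
|---|---|---|---|
| 1% to 2% | 6% | 1% | 3 |
| 2% to 4% | 11% | 4% | 6 |
| 5% to 10% | 27% | 19% | 15 |

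**5. Events against model terms.** Treatment, baseline peak VO2, age, gender, systolic pressure, diastolic pressure and BMI make seven fixed effects, and the two interactions make nine. The random effect could have up to 64 practices. The chance that an arm has no conversions is (1 − p)^100, so the chance that at least one arm has none is 1 − [1 − (1 − p)^100]².

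- At 1% in both arms: (0.99)^100 = 0.366, giving 60%.
- At 2% in both arms: (0.98)^100 = 0.133, giving 25%, with only 4 conversions expected in total.

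Splitting by stratum makes the counts smaller still.

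**The case against.** The strongest reply is that the power sentence is conditional on published magnitudes and closes a section about other endpoints, so it is loosely scoped and makes no false numerical promise about rhythm. No stated figure for sinus rhythm exists to be wrong, and the four calculations in step 1 are sound. That is right as far as it goes. It does not save the sentence, which makes no exception and depends, for rhythm and EQ-5D, on published effects that are not cited.

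A reader might infer three stronger points that the documents do not support.

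- **That there will be too few conversions.** No conversion rate is given. Rarity is a reasonable inference from the definition of permanent AF, but a large enough gain would still reach 80% power.
- **That EQ-5D is underpowered.** It is uncalculated, and 100 per arm would suffice for a standardised difference of 0.40.
- **That a linear model is forced on a binary outcome.** Section 13.1 allows non-linear mixed models, so a logistic one is open. The difficulty is sparse events, which a logistic form does not cure.

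It is also fair to say that fallback methods for separation usually belong in the statistical analysis plan, which is not at hand. The point here is limited to what the protocol does prescribe: interactions and per-stratum models for all secondary endpoints. Sinus rhythm is the last secondary endpoint listed, and neither the sample size nor the primary analysis depends on it.

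**Conclusion.** The point holds in this limited form. The statement of at least 80% power is unsupported for return to sinus rhythm and EQ-5D, and that conclusion needs no assumption about rates. For sinus rhythm the claim is unlikely to hold for modest effects: at assumed placebo rates of 0% to 5%, 80% power needs an absolute gain of about 5.5 to 12 percentage points, and a doubling has 6% to 27% power. These figures rest on 100 evaluable per arm, a two-sided 5% uncorrected chi-square test and the assumed rates. The prescribed mixed model is ill-suited to this endpoint if conversions are as few as those rates imply. The primary analysis and the sample size are unaffected.

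**What to change.** In the sample-size conclusion, limit the power statement to peak VO2, 6-minute walk, E/e' and MLWHFQ. State that no power was calculated for sinus rhythm or EQ-5D, and that a null rhythm result is not evidence of no effect. Admissions can be added once the 15% reduction is defined and the calculation shown to hold.

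In section 13.1, exempt sinus rhythm from the covariate, interaction, random-effect and per-stratum mixed models. Report the counts per arm and the risk difference with a confidence interval suited to sparse data, plus one treatment-only sparse-event method, for example Firth-penalised logistic regression or an unconditional exact test. If Fisher's test is chosen, acknowledge that it is conservative: at true rates of 2% or 5% in both arms its actual size is about 0.5% or 2%, and it has the lower power shown above.

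The cost is wording only: a less favourable power statement, and loss of covariate adjustment for this one endpoint.

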## **14. TRIAL ORGANISATIONAL STRUCTURE**

### **14.1 Sponsor**

The University of Birmingham are the sponsors of this trial.

### **14.2 Coordinating Centre**

The day-to-day management of the trial will be coordinated by the Primary Care Clinical Research and Trials Unit (PC-CRTU, fully registered by the NIHR as a trials unit) at the University of Birmingham.

### **14.3 Trial Management Group**

The *Trial Management Group* (CI, PI, trial team, members of PC-CRTU) will meet regularly (usually monthly, with additional meetings as required) to ensure successful implementation of the trial. They will monitor participant recruitment; any departure from the expected recruitment rate will be dealt with according to the specific issues discovered. For example, GPs may need clarification of inclusion criteria and we will visit the practices to improve performance.

The Chief Investigator (CI) takes overall responsibility for the conduct of the trial. The Principal Investigator (PI) will take responsibility for all activity conducted at site. Any delegated responsibility will be documented on the site delegation log. It is the PI's responsibility to ensure that staff are appropriately trained to perform the tasks delegated to them, and that training is documented and the delegation log completed.

The research team comprises a group of experts in particular fields closely related to the project core, such as world leading clinical authorities in AF and HF ([name] [CI] and [name] [co-investigator]), a postdoctoral clinician-expert in human molecular biology related to the project field, with extensive experience in clinical and research echocardiography ([name] [co-investigator and PI at site]), an expert in primary care and heart failure ([name]), quality of life and trials ([name]), a trial statistician ([name]), an expert in exercise testing ([name]), and a participant and public involvement representative with extensive experience ([name], Doctor in Physics).

---

|                          |            |               |            |       |          |
|--------------------------|------------|---------------|------------|-------|----------|
| Trial name:              | IMPRESS-AF |               |            |       |          |
| Protocol version number: | 6.0        | version date: | 12/10/2015 | Page: | 48 of 67 |

### 14.3.2 Data Monitoring and Ethics Committee

Please see section 1.27 for information on the structure and responsibility of the independent DMEC.

## 14.4 Finance

This is a clinician-initiated and clinician-led trial funded by the NIHR (National Institute for Health Research).

## 15. ETHICAL CONSIDERATIONS

The trial will be performed in accordance with the recommendations guiding physicians in biomedical research involving human subjects, adopted by the 18th World Medical Association General Assembly, Helsinki, Finland, June 1964, amended at the 48th World Medical Association General Assembly, Somerset West, Republic of South Africa, October 1996 (website: <http://www.wma.net/en/30publications/10policies/b3/index.html>).

|                          |            |               |            |       |          |
|--------------------------|------------|---------------|------------|-------|----------|
| Trial name:              | IMPRESS-AF |               |            |       |          |
| Protocol version number: | 6.0        | version date: | 12/10/2015 | Page: | 49 of 67 |

---

The trial will be conducted in accordance with the Research Governance Framework for Health and Social Care, The Medicines for Human Use (Clinical Trials) Regulations and subsequent amendments and the Data Protection Act 1998 *and Human Tissue Act 2008*. This trial will be carried out under a Clinical Trial Authorisation. The protocol will be submitted to and approved by the main Research Ethics Committee (REC) prior to circulation.

Before any participants are enrolled into the trial, the Principal Investigator at each site is required to obtain local R&D approval/assurance. Sites will not be permitted to enrol participants until written confirmation of R&D approval/assurance is received by the PC-CRTU trials team.

It is the responsibility of the Principal Investigator to ensure that all subsequent amendments gain the necessary local approval. This does not affect the individual clinicians' responsibility to take immediate action if thought necessary to protect the health and interest of individual participants.

---

|                          |            |               |            |       |          |
|--------------------------|------------|---------------|------------|-------|----------|
| Trial name:              | IMPRESS-AF |               |            |       |          |
| Protocol version number: | 6.0        | version date: | 12/10/2015 | Page: | 50 of 67 |

---

## **16. CONFIDENTIALITY AND DATA PROTECTION**

Personal data recorded on all documents will be regarded as strictly confidential and will be handled and stored in accordance with the Data Protection Act 1998.

Participants will always be identified using only their unique anonymised participant number on the Case Report Form and correspondence between PC-CRTU and the participating site.

The Investigator must maintain documents not for submission to PC-CRTU (e.g. Participant Identification Logs) in strict confidence. In the case of specific issues and/or queries from the regulatory authorities, it will be necessary to have access to the complete trial records, provided that participant confidentiality is protected.

The trial team will maintain the confidentiality of all participants' data and will not disclose information by which participants may be identified to any third party without prior consent from the participant. Representatives of the IMPRESS-AF trial team, regulatory authorities and sponsor may be required to have access to participant's notes for quality assurance purposes but participants should be reassured that their confidentiality will be respected at all times.

---

|                          |            |               |            |       |          |
|--------------------------|------------|---------------|------------|-------|----------|
| Trial name:              | IMPRESS-AF |               |            |       |          |
| Protocol version number: | 6.0        | version date: | 12/10/2015 | Page: | 51 of 67 |

---

## **17. INSURANCE AND INDEMNITY**

University of Birmingham employees are indemnified by the University insurers for negligent harm caused by the design or co-ordination of the clinical trials they undertake whilst in the University's employment.

In terms of liability at a site, NHS Trust and non-Trust hospitals have a duty to care for participants treated, whether or not the participant is taking part in a clinical trial. Compensation is therefore available via NHS indemnity in the event of clinical negligence having been proven.

The University of Birmingham offers indemnity for non-negligent harm. The University of Birmingham is independent of any pharmaceutical company, and as such it is not covered by the Association of the British Pharmaceutical Industry (ABPI) guidelines for participant compensation.

---

|                          |            |               |            |       |          |
|--------------------------|------------|---------------|------------|-------|----------|
| Trial name:              | IMPRESS-AF |               |            |       |          |
| Protocol version number: | 6.0        | version date: | 12/10/2015 | Page: | 52 of 67 |

---

**18. PUBLICATION POLICY**

Results of this trial will be submitted for publication in a peer reviewed journal. The manuscript will be prepared by [name] and authorship will be determined by mutual agreement. This will include all co-investigators providing that they meet authorship criteria plus any other authors by agreement.

Any secondary publications and presentations prepared by Investigators must be reviewed by the CI. Manuscripts must be submitted to the NIHR. Authors must acknowledge that the trial was performed with the support of sponsor (*University of Birmingham*) and the NIHR. Intellectual property rights will be addressed in the "*Clinical Trial Site Agreement*" between Sponsor and site.

---

|                          |            |               |            |       |          |
|--------------------------|------------|---------------|------------|-------|----------|
| Trial name:              | IMPRESS-AF |               |            |       |          |
| Protocol version number: | 6.0        | version date: | 12/10/2015 | Page: | 53 of 67 |

